### Data collection

A secure Research Electronic Data Capture (REDCap) [18] project will be developed that will enable consistent data entry online using mobile connectivity. Standardised questionnaires will be used to collect data electronically in a robust fashion enabling patients to be identified through unique identifier or combination of demographic information such as names, surnames, date of birth, sex and other personal identifiers (e.g. South African identity number) already captured in TIER.Net database.

Before data collection begins, the REDCap will be thoroughly tested and subjected to a range of checks culminating in the entry of data for a group of ‘dummy’ patients, and this will be followed by extraction of dummy dataset by a research data manager and derivation of key study outcome measures by the study statistician to ensure data fields and response coding are clear. After all checks, the database is ‘signed off’ by the research data manager and statistician.

Once data entry has begun periodic validation and management checks will be performed using Pentaho Data Integration to assess data completeness, rate of recruitment and data consistency. Exception reports will be created, and issues raised will be queried with the study coordinator.

#### Health system gap

The following data will be extracted from chart review into REDCap to document if (i) viral load was actually not measured as evidenced by a lack of documentation of this in the clinical charts and in TIER.Net (ii) there was documentation of a blood draw for VL and the date of the test (iii) results were filed and entered into the patient charts although not captured in TIER.Net (iv) there was evidence in patient chart that test was done but no results filed (v) VL results and date present in TIER.Net but not filed in patient charts.

All data collected from clinical chart reviews will be centrally stored in a master MONART database located at Africa Health Research Institute. This database will integrate data collected from clinical charts reviews, hospital information management system (HIS), ClinicLink and TIER.net. Database rules and constraints will be added and enforced on the master database to ensure that only valid data is stored in the database.

A study dashboard will be developed to assist the operational teams monitor the progress of the study.

#### Evaluation of the intervention impact

TIER.Net has information on HIV-positive individuals on ART including unique South African Identification number, age, sex, date of ART initiation, viral load results and dates, CD4 count results and dates, type of ART regimen, status of the individual (whether still in care, lost to follow up or dead), and dates of clinic appointments. The clinical charts of the 150 participants per clinic who are in the evaluation cohort will be reviewed to extract these baseline data for entry into REDCap. These will be repeated after each participant has completed 12 months of follow up in their clinic/cluster to capture documentation of VL being measured, test data and the results of the VL. These data will be used to evaluate the impact of the intervention on VLM and virological suppression, and on the treatment failure cascade. Data on all clinic visits irrespective of reason for the visit will be extracted from ClinicLink. These will be used to describe patterns of health care use among the trial population. HIV-positive individuals receiving care in the clinics are not the recipients of the quality improvement interventions, which will be focussed on the nurses and systems for delivering care. Hence, interim visits for any intercurrent illness by patients will be managed as per standard clinical care and will not be routinely reported as adverse events.

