**Methods/design:**

The study will evaluate the effectiveness of the QIP compared to current care for improving VLM and virological suppression using an effectiveness implementation hybrid type 3 design. This will use a cluster-randomised design with the primary healthcare clinics as the unit of randomisation with ten clinics randomised in a 1:1 ratio to either the intervention or control arm. We will enrol 150 HIV-positive individuals who had been on ART for ≥ 12 months from each of the ten clinics (750 in 5 intervention clinics vs. 750 in 5 control clinics) and follow them up for a period of 12 months. The primary outcome is the proportion of all patients who have a viral load (VL) measurement and are virally suppressed (composite outcome) after 12 months of follow up. Secondary outcomes during follow up include proportion of all patients with at least one documented VL in TIER.Net, proportion with VL ≥ 50 copies/mL, proportion with VL ≥ 1000 copies/mL (virological failure) and subsequent switch to second-line ART.

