## Background

Antiretroviral therapy (ART) scale-up in sub-Saharan Africa (SSA) has been rapid with an estimated 16.4 million individuals on ART by the end of 2018 [1]. The increased expansion in the indication for ART use would result in earlier initiation of treatment and if adherence is suboptimal, could lead to virological failure and the likely development of drug resistance. The likelihood of transmission of resistant virus will depend on ART coverage, duration of ART roll-out and the proportion and absolute numbers of individuals with virological failure [2–4]. Conditions that would influence transmission of resistant virus include proportion of failures with resistant virus, time spent on failing regimen, viral load (VL) of patients with resistant virus, fitness of the resistant virus and the transmission probability compared with ART-naïve individuals [2]. The availability of viral load monitoring (VLM) in resource-rich countries, means individual failing treatment are identified early and switched to alternative suppressive ART. In contrast, many sub-Saharan African countries rely on World Health Organisation (WHO) immunological and clinical criteria for identifying treatment failure which has poor sensitivity and specificity [5]. In settings where there is availability of VLM, their effectiveness has been hampered by poor adherence to monitoring guidelines by healthcare providers [6].

South Africa has the biggest HIV treatment programme in the world with 7.7 million individuals living with HIV and 62% currently receiving ART within a stretched health system [1]. VLM has been part of the public ART programme since roll-out in 2004 and requires people living with HIV (PLHIV) initiating ART to have a VL measured at 6 months and 12 months after ART initiation and 12-monthly thereafter if virologically suppressed [7, 8]. Those with a VL ≥ 1000 HIV-1 RNA copies/mL should be retested after 3 months of adherence counselling support, and then either retained on first-line therapy if re-suppressed or switched to second-line therapy if VL ≥ 1000 copies/mL [7].

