However, little is known about how these VL guidelines are being used in clinical decision-making in public ART programmes in SSA. In formative research utilising an electronic database, the Three Interlinked Electronic Register (TIER.Net) [9], of a programmatic ART cohort in rural KwaZulu-Natal, we observed infrequent VLM and sub-optimal management of virological failure. The study showed that only 34% of patients had a viral load documented after 12 months on ART. Only 20% of individuals in the cohort were confirmed to have virologic re-suppression or change to second line therapy after virologic failure, and those who changed therapy did so a median of one year after virologic failure [10]. With the expansion in the indications for ART use [11], such delays are likely to have significant deleterious individual and public health impacts through effects on patient morbidity, accumulation of drug resistance [12–14], and persistent risk of HIV transmission in the setting [15].

Findings from this formative research was presented in a series of workshops to healthcare providers, policy makers, researchers and community representatives using good participatory approaches with a view to co-produce health system interventions to address poor VLM. This protocol describes the proposed interventions and their evaluation. We hypothesise that a staff-centred quality improvement package (QIP) and technological augmentation of an existing electronic ART database (TIER.Net) would result in optimal VLM of patients on ART, prompt clinical management of virological failure and an overall improvement in virological suppression.

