##### Secondary outcomes

Proportion of all patients with at least one documented VL in TIER.Net during the trial follow up.Proportion with VL ≥ 50 copies/mL during follow upProportion with VL ≥ 1000 copies/mL during follow up (virological failure)Among patients with VL ≥ 1000:Proportion with a repeat test within 3 monthsTime from first VL ≥ 1000 copies/mL to repeat VL.Proportion switching to second-line ART after two consecutive VL ≥ 1000 copies/mL measured ≤ 3 months apartProportion completing the treatment failure cascade (VL < 50 copies/mL on repeat testing or switch to second line ART)Cost-effectiveness of the intervention compared to current care with respect to the primary outcome (viral suppression at 12 month follow-up) and two secondary outcomes (proportions of patients with VL ≥ 50 copies/mL and VL ≥ 1000 copies/mL)Acceptability, fidelity, adaptation and contexts in the implementation of the interventions

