### Trial procedures and timelines

We will pilot the interventions over 3 months to address any issues raised and deliver further training to the nurses or adaptation of the technology if required (Fig. 2). Patients attending for their routine clinic visits over a three month period, which we estimate is the time required for at least 150 participants to pass through each clinic, will be included in the evaluation cohort and followed up for a period of 14 months to allow a 2 month window for appointment reschedules etc.

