#### Evaluation of the trial intervention

The effect of the intervention on the primary outcome (proportion of patients with VL suppression) will be estimated using a two-stage approach based on cluster (i.e. clinic)-level summaries [19]. The cluster-level approach, although less statistically efficient than methods based on individual level regression, is more robust when there are a relatively small number of clusters. Briefly, in the first stage, the proportion with VL suppression in each clinic will be calculated, and logarithmically transformed. In the second stage, the cluster-level summaries will be compared using a stratified t-test to test the null hypothesis of no intervention effect. Since equal numbers of clinics will be allocated to the 2 arms within each stratum, the unadjusted risk ratio (RR) for the intervention effect will be calculated as the ratio of geometric mean proportion with VL suppression for the 5 clusters in each arm. The 95% confidence interval (CI) will be calculated with the variance estimated from the residual mean square in a two-way analysis of variance of the log proportions on stratum and trial arm, incorporating a stratum by trial arm interaction. An adjusted analysis based on cluster-level summaries may also be done to account for covariate imbalance at baseline, using a similar two-stage process. All covariates will be pre-specified in a detailed analysis plan. In the first stage, an individual-level logistic regression will be done, including terms for stratum and all covariates except the intervention effect, and ignoring clustering. After fitting the regression model, a residual for each cluster will be calculated as the ratio of the observed to the predicted number of events. If the intervention has no effect, the residuals of the two arms should be similar on average. In contrast, if the intervention has an effect, we expect the residuals to differ systematically. Therefore, in the second stage, we will compare the residuals between the trial arms using the methods described above; residuals will be log transformed for the analysis. Analysis of the intervention effect on the secondary outcomes will be done using the same approach. A detailed statistical analysis plan will be prepared before to data analysis.

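### Cascade completion and switching after VL ≥ 1000 have no observation horizon from failure, so their proportions mix the timing of detection with the management of failure

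*Protocol article*

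**What the plan says.** **Follow-up is counted from enrolment, with two lengths.** The Abstract (Methods/design) says the trial will enrol patients and "follow them up for a period of 12 months". Data collection, Evaluation of the intervention impact, says of the chart reviews: "These will be repeated after each participant has completed 12 months of follow up in their clinic/cluster". It uses the resulting data for the effect on VL monitoring and suppression and "on the treatment failure cascade". Trial procedures and timelines says patients are "followed up for a period of 14 months to allow a 2 month window for appointment reschedules etc".

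**The outcomes start at a high VL.** Among patients with VL ≥ 1000, Secondary outcomes lists:
- a repeat test within 3 months;
- the time from first VL ≥ 1000 "copies/mL to repeat VL";
- switching after two consecutive high VLs at most 3 months apart;
- cascade completion, meaning VL < 50 on repeat testing or a switch.

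Only the first has a window from failure. The switch outcome limits the gap between the two VLs, not the time to the switch. Cascade completion has no limit.

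**Analysis.** Under Evaluation of the trial intervention: "Analysis of the intervention effect on the secondary outcomes will be done using the same approach". That approach compares log-transformed clinic proportions. A detailed analysis plan is promised and is not shown.

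**Time scales in Background.** Patients with VL ≥ 1000 "should be retested after 3 months of adherence counselling support". In the formative cohort, "those who changed therapy did so a median of one year after virologic failure".

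**The concern.** Suppressed patients are tested every 12 months (Background), so a first VL ≥ 1000 can occur at any time in follow-up. With data closing at a fixed time from enrolment, a patient who fails early is watched for most of a year and one who fails late for weeks. In a simple proportion, both count equally, and the late failure is likely to appear as not switched or not completed.

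If timing were the same in both arms, this would only lower both proportions. But the intervention is meant to find sooner the patients who are due a VL (Augmentation of TIER.Net with a dashboard system). If it does, its failures are detected earlier and observed longer. Prompt management of failure is part of the trial's hypothesis, so an artefact of timing could be read as one of the claimed benefits.

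**Working it through.** **The plan's own figure.** None is given for these outcomes. The only power statement is for the primary outcome: 50% against 77%, 5 clinics per arm, m = 150, k = 0.20, power 80%. With two-sided α = 0.05 (assumed):

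c = 1 + (1.96 + 0.84)² × [0.5×0.5/150 + 0.77×0.23/150 + 0.20²×(0.5² + 0.77²)] / 0.27² = 4.94 clinics per arm.

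Five clinics give 80.6% power, so the figure reproduces. Nothing below affects it.

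**Assumptions.** The first VL ≥ 1000 occurs at month T after enrolment, data close at month L (12 or 14), and the delay to action is exponential with the same median in both arms. Any difference between arms then comes from timing alone. The distributions of T are assumed, because the protocol gives none.

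**Share of first failures with under 3 months left.** T is uniform over 0–12, or early- or late-weighted (triangular).

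| T | L = 12 | L = 14 |
|---|---|---|
| Early | 6% | 0.7% |
| Uniform | 25% | 8.3% |
| Late | 44% | 16% |

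**Switching, no horizon.** Median delay 12 months, λ = ln 2/12 per month. If the time left is uniform from a to b months, the observed proportion is 1 − (e^(−λa) − e^(−λb)) / (λ(b − a)).

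- L = 12, T over 0–12 (0 to 12 months left): 1 − (1 − 0.5)/0.6931 = 27.9%
- L = 12, T over 0–8 (4 to 12 left): 1 − (0.7937 − 0.5)/0.4621 = 36.4%. Ratio 36.4/27.9 = 1.31
- L = 14, T over 0–12 (2 to 14 left): 1 − (0.8909 − 0.4454)/0.6931 = 35.7%
- L = 14, T over 0–8 (6 to 14 left): 1 − (0.7071 − 0.4454)/0.4621 = 43.4%. Ratio 43.4/35.7 = 1.21

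**Any retest by data close, no horizon.** Median delay 3 months, simulated.

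| T | L = 12 | L = 14 |
|---|---|---|
| Early | 80% | 87% |
| Uniform | 66% | 79% |
| Late | 52% | 70% |
| RR, early vs uniform | 1.21 | 1.11 |
| RR, early vs late | 1.53 | 1.25 |

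**Retest within 3 months, horizon stated.** Same delay, so the true value is 50% in both arms.

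| T | L = 12 | L = 14 |
|---|---|---|
| Early | 49.2% | 50.0% |
| Uniform | 44.5% | 49.5% |
| Late | 39.8% | 49.0% |
| RR, early vs uniform | 1.11 | 1.01 |
| RR, early vs late | 1.24 | 1.02 |

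Counting only patients with at least 3 months left returns 50% in every case, so RR = 1.00.

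**The case against.** **A fixed 12-month cut.** A reader might infer that data close at exactly 12 months and that late failures have no time at all. The documents do not support this. The chart-review sentence sets an earliest date, and Trial procedures and timelines gives 14 months. With 14 months, a first high VL at month 10 has its 3-month retest at month 13, inside follow-up, and re-suppression on that test completes the cascade without a switch. Time is reduced for late failures and close to nil only near the data close.

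**Size.** A reader might take 1.31 as the expected bias. It is not. The shift to months 0–8 is invented. The one-year median covers only those who changed therapy, and in the same cohort only 20% had confirmed re-suppression or a change. If at most 20% ever switch, the 12-month figures become 0.20 × 27.9 = 5.6% and 0.20 × 36.4 = 7.3%: the same ratio, but a gap under 2 points. The model also starts the clock at the first high VL, whereas the switch outcome requires two, so a patient not yet retested may not enter its denominator.

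**Direction.** The 3-month pilot may clear some overdue VLs before enrolment, and champions who trace and recall patients could add late-detected failures. The direction is an inference.

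**Required follow-up.** The historic one-year delay is what the intervention aims to shorten. The protocol does not make it a minimum observation time.

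**Left to the analysis plan.** Denominators and censoring commonly are, and their absence here is no fault. What stands is that the outcome definitions, the collection point and the method are stated here. A later plan can restrict or censor, but it cannot recover events after the data have been extracted.

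**Conclusion.** The point holds in limited form. Cascade completion and switching are counted to a point fixed from enrolment, have no horizon from failure, and are to be compared as simple proportions. They can therefore differ between arms through detection timing alone. Under the stated assumptions the spurious ratio for switching is about 1.31 at a 12-month close and 1.21 at 14 months. These figures show that the mechanism is not negligible; they do not predict its size or sign in this trial.

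The 3-month retest proportion already has a horizon. It is materially affected only if data close at 12 months (1.11 to 1.24), and little at 14 (1.01 to 1.02). The primary outcome is not touched. This concerns secondary outcomes and should be corrected before data are extracted.

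**What to change.** 1. Reconcile the 12 and 14 months, and state one data-close point for the outcomes after VL ≥ 1000.
2. Define cascade completion and switching over one fixed observation horizon from the first VL ≥ 1000, the same in both arms.
3. Preferably, continue passive TIER.Net extraction for patients with VL ≥ 1000 until that horizon is reached. TIER.Net holds VL dates and regimen. Because VLs enter it by automatic import in one arm and by hand in the other, the extension should use the same sources in both arms, including charts if the main extraction relies on them.
4. Otherwise, limit the denominator to patients whose full horizon is observable, or use time-to-event methods with censoring at data close, summarised by clinic. The time-to-repeat-VL outcome needs a censoring rule in any case.
5. Report the timing of first VL ≥ 1000 by arm, so that readers can judge any remaining imbalance.
6. Before setting the horizon, reconcile the retest intervals: after 3 months (Background), at least 3 months apart (dashboard definition of confirmed failure), and within or at most 3 months (Secondary outcomes).

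**Cost.** Option 3 needs one later extract for a small subgroup, with no new patients or visits. Restricting the denominator loses patients: under uniform timing and a 12-month close, 3/12 = 25% for a 3-month horizon and 6/12 = 50% for a 6-month one. It also still conditions on detection after randomisation, which the intervention may affect.

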### Trial procedures and timelines

We will pilot the interventions over 3 months to address any issues raised and deliver further training to the nurses or adaptation of the technology if required (Fig. 2). Patients attending for their routine clinic visits over a three month period, which we estimate is the time required for at least 150 participants to pass through each clinic, will be included in the evaluation cohort and followed up for a period of 14 months to allow a 2 month window for appointment reschedules etc.

**Fig. 2 Fig2:**

Study timelines

### Data management

Due to data protection regulation, AHRI will act as data controller for the project. UCT and UoS will be data processors but will only process anonymised data for the purpose of analysis. It will be the responsibility of the data custodian based at AHRI to ensure that data access is consistent with terms of the AHRI Data Access Policy and ethical approval obtained for this protocol.

Data will be stored on industry-standard relational databases with data integrity and user authentication for access control. Data will be replicated on at least a daily basis to the Durban site of the Institution to provide secure offsite storage of data. Transactional logs will be backed up every 30 min to enable recovery of data in the event of equipment failure.

All users of the MONART electronic data collection system (REDCap) and database will be authenticated through individual passwords with minimum complexity and regular change rules (passwords must be at least eight characters, with a mix of small and capital letters, at least one numeric or non-alphabetic digit and changed at least every 45 days). The Institution use industry standard malware and intrusion detection with regular penetration tests by a reputable external security audit company.

Both at the Institute and for the clinic-based data collection, a client–server architecture will be implemented where data is not stored on laptops or local workstation, but only on a central server with restricted physical access. Specifically, at the clinics the local server will be enclosed in a tamper-proof enclosure kept under lock and key.

Once data have been stored in the MONART databases, they will become the responsibility of the head of research data management. Research data management will regularly assess data quality and implement corrective measures to ensure data quality. At the end of the study, anonymised analytical datasets will be created, documented and archived on the AHRI data repository. A digital object identifier (DOI) will be created and added on the dataset documentation for reference purpose. Research data management will administer a data repository that will contain all datasets required for analysis for the trial. They will ensure that the repository has access control measures that enforce the data access criteria determined by the study data steering committee. Access to the datasets will be granted to those who meet minimum requirements set out by the study data steering committee.

All correspondence relating to this project will be kept in appropriate file folders. Any confidential patient or site information will be kept in secure, limited access locations. Records of participants, other source documents, pertaining to the study will be kept on file for a period of 10 years per South African Good Clinical Practice guidelines (SA GCP).

